#### Informed consent and withdrawal

Informed consent will be on the opening page of the online survey. Participants volunteering to participate in interviews and group discussions will also receive the consent form stating that the conversations will be audio recorded. The consent form will clearly explain what participation entails, that it is possible to withdraw from the study, and that participants can request that their own data be removed from the study until the time the analysis is conducted. A final withdrawal date will also be provided in the information sheet, after which participants may no longer withdraw their data from the study.

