##### Interviews

We will conduct formative research interviews to understand context but not to assess impact. A guide to interview participants and “Youth in Action” staff has been developed based on field work conducted in previous projects, where several of the authors participated, that studied the relation between mental health and poverty (24). The guide seeks to find the mental health resources that are available to our population and disposition to seek or recommend seeking help their willingness to participate in a mental health program. Participants and staffers will be encouraged to discuss these themes presented in the Appendix 1. The core of the discussion will be formative research that focuses on their understanding of mental health access to mental health services, and barriers/facilitators to access a mental health intervention. Questions will focus on ways to overcome stigma and recommendations on forms to generate acceptability of language related to mental health themes that will impinge on the willingness to answer our surveys. The invitations to participate in the intervention where we plan to outline the stepped care program will be co-written by JeA youth and staff to optimize engagement.

We will conduct semi-structured one-to-one interviews with 8 JeA staff to explore their experiences supporting young people with mental health issues and their views on potential barriers and facilitators to embedding the intervention in the JeA program. We will also carry 10 one-to-one interviews with young people who are beneficiaries of the JeA program to explore their views around mental health and their experiences of seeking or providing (to friends, for example) support for emotional distress and mental well-being. We will include young people enrolled in the JeA program, which will include youth with different characteristics, e.g., displaced people, victims of the armed conflict, indigenous people, and some who do not belong to any of these groups. The recruitment of these participants will be done by the regional staff of Youth in Action. They will provide us with a list of potential beneficiaries who are interested on participating and the research team will randomly select ten of them.

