#### Phase 3 (18 months)

During Phase 3, we will pilot the intervention to determine its feasibility, acceptability, efficacy, and usefulness in ‘real settings’. Results will inform if the intervention improves clinical, educational and employment prospects among those who use it. A sample of beneficiaries studying in our areas of interest will be invited to participate in a survey containing measures of mental health human capital. All those beneficiaries scoring above cut-off points will be automatically invited to access the intervention, and anyone suspected at risk will be offered support and referral to health services.

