##### Intervention

The study will pilot a stepped-care mental health program that aims to be structured, brief and includes evidence-based components. The digital intervention will not be developed by the research team. Instead, we will use a third-party platform (SilverCloud®) a virtual mental health platform with eight modules with different tools for comorbid depressive and anxiety symptoms. This platform has been adapted for use by student populations that mainly attend private universities in Colombia and has proven to be effective (25).

This program is designed to facilitate the participants’ social and labor insertion. The intervention will target depression, anxiety, PTSD, and comorbidities. Participants from the intervention sites will be classified in four levels of severity (asymptomatic, mild, moderate, and severe) according to their scores in these three dimensions encompassing access to a mental-health digital platform and individualized care. They will be offered differential attention strategies (see Figure 2). We will use a transdiagnostic stepped-care intervention program, in which three levels of attention will be in place to respond to the severity of the symptoms as determined by three screening questionnaires encompassing access to a mental-health digital platform and individualized care. This strategy has been planned to provide individualized care for those in severe conditions and considering the high degree of comorbidity documented in conflict zones. The protocol also considers the number of sessions we anticipate will be amenable to our participants. Participants with moderate and mild symptoms will also have access to the digital platform. People with moderate symptoms will have a coach to monitor their progress while the platform is available; people with mild conditions will only be offered the platform. Unlike previous mental health initiatives, we intend to ascertain how to foster the acceptability of a digital strategy, in our initial co-design phase, and the acceptability of personalized virtual sessions with our psychologists.

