#### Study design

Our study is based on a cross-over design, whereby participants in three treatment municipalities (Florencia, Santa Marta, and Valledupar) will be offered the intervention, while participants in four control municipalities (Apartadó, Buenaventura, Ciénega, and San Andrés de Tumaco) will serve as control. Due to ethical reasons, we must offer the intervention to beneficiaries in the control municipalities following the period of intervention in the treatment group. Control municipalities will thus receive the intervention once the two post-treatment measures are taken.

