### Quantitative analysis of impact

Our primary aim will be to assess the impact of the intervention on our mental health and human capital outcomes. We will use regression analysis with a difference-in-differences design, which compares changes in outcomes before and after intervention measures across participants in treatment and control areas. This approach considers human capital as an outcome embodied in individuals by exploring the variation in individual knowledge (cognitive skills captured by academic performance) and individual abilities (non-cognitive skills acquired as life competencies). Thus, we will look at the magnitude of mental health-based rehabilitation on young adult students across different dimensions of mental health (depression and anxiety, fundamentally), which is considered beneficial due to human capital accumulation.

Since individual observations will be collected in different regions, we will adjust for clustered data. In the absence of treatment randomization that assures that treatment and control groups are exchangeable, this quasi-experimental design helps us to control for time-invariant differences between treatment and control areas by focusing on changes, rather than levels, in outcomes. To address bias from time-varying confounders, we will incorporate controls for time-varying factors in all analyses. We will all report the prevalence of depression, anxiety, and PTSD, along with their commodities and the effectiveness outcome, which will be the proportion of participants with a reduction in their baseline symptoms. To determine the changes in human capital, we will use both administrative and survey data that measure continued JeA program enrolment, accumulated grade point average, and self-reported hours dedicated to study. This will be carried out in STATA-19.

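### Respondents probably know before the baseline survey whether care comes soon or late, so baseline scores may be raised more in treated sites and pass into the difference-in-differences as benefit

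*Protocol article*

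**What the plan says.** **Allocation.** Under Study design, "participants in three treatment municipalities (Florencia, Santa Marta, and Valledupar) will be offered the intervention", and four other named municipalities serve as controls. Quantitative analysis of impact acknowledges the setting: "In the absence of treatment randomization that assures that treatment and control groups are exchangeable".

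**Consent.** Under Informed consent and withdrawal, "Informed consent will be on the opening page of the online survey". The same section adds: "The consent form will clearly explain what participation entails".

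**Use of the baseline score for care.** Under Phase 3, "All those beneficiaries scoring above cut-off points will be automatically invited to access the intervention". Under Intervention, "Participants from the intervention sites will be classified in four levels of severity", and the level decides between the platform alone, the platform with a guide, and the platform with a guide plus a psychologist. Controls receive nothing until their measures are complete, then the self-guided platform and an email (Intervention; Study design). Apart from referral of those at risk, no grading by score is described for them.

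**Use of the baseline score for analysis.** The same survey is given before the intervention and at two follow-ups (Screening questionnaire). The difference-in-differences "compares changes in outcomes before and after intervention measures across participants in treatment and control areas", and the effectiveness outcome is the proportion whose symptoms fall from baseline.

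**Invitations.** Under Interviews, "The invitations to participate in the intervention where we plan to outline the stepped care program will be co-written by JeA youth and staff". The article does not say whether these precede the baseline survey or differ by arm.

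**The concern.** One self-reported score does two jobs. In treated sites it opens the door to care and sets its intensity. In the analysis it is the value from which change is measured. It is collected when the respondent's arm is already settled by where they live, and after a consent page that would ordinarily say whether help comes now or months later.

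Two things may follow. People who are distressed at that moment have more reason to enter where care is immediate. Those who enter have more reason to score high where the score decides what they are offered.

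Difference-in-differences removes stable differences between areas. It does not remove a temporary rise at baseline that is larger in one arm: that rise falls away by follow-up and is read as improvement. The time-varying covariates mentioned in the analysis section would not capture it, because they do not measure the motive to enter or to over-report. Every self-reported symptom outcome is exposed, and a baseline collected this way cannot be repaired by later analysis.

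**Working it through.** **Yardstick.** Sample size gives f = 0.125. For two equal groups d = 2f = 0.25, as stated. A two-sided 5% comparison with 80% power at d = 0.25 needs 252 per arm, 504 in total, close to the stated 501; this match leaves the stated ICC out. The yardstick below is 0.25 SD.

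**Inputs the article does not give, so assumed.** Odds ratio for entry per SD of current distress, treated areas only: 1.2 to 2.0. Correlation between waves, r: 0.5 to 0.8. Response in treated areas: about 13% or 50%. Over-reporting: 0.5 to 1 PHQ-9 point, SD 5 to 6. The same cut-off in both arms, at the survey mean. No true effect.

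**1. Differential entry.** Let x be the standardised baseline score and y = r·x + √(1 − r²)·e the follow-up score. Expected change given x is −(1 − r)·x, so

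false benefit = (1 − r) × (m_T − m_C),

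where m is the mean baseline score of entrants above the cut-off. Controls enter regardless of distress: m_C = φ(0)/0.5 = 0.798. Treated entry is logistic in x with slope ln(OR); intercept −2 gives 12% to 14% response and intercept 0 gives 50%.

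| OR, r | m_T at about 13% | False benefit | m_T at 50% | False benefit |
|---|---|---|---|---|
| 1.2, 0.8 | 0.857 | 0.2 × 0.059 = 0.012 SD | 0.828 | 0.2 × 0.030 = 0.006 SD |
| 1.5, 0.6 | 0.931 | 0.4 × 0.133 = 0.053 SD | 0.858 | 0.4 × 0.060 = 0.024 SD |
| 2.0, 0.5 | 1.016 | 0.5 × 0.218 = 0.109 SD | 0.883 | 0.5 × 0.085 = 0.042 SD |

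Divided by 0.25, the range is 5% to 44% of the planned effect at about 13% response and 2% to 17% at 50%. The response rate matters as much as the odds ratio.

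**2. Over-reporting in treated sites only, gone by follow-up.** The shift b runs from 0.5/6 = 0.083 SD to 1/5 = 0.20 SD. With the cut-off applied to the reported score, the mean true score of entrants is m(b) = φ(b)/Φ(b), and

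false benefit = b − (1 − r) × (m(0) − m(b)).

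- b = 0.083, r = 0.5: 0.083 − 0.5 × (0.798 − 0.746) = 0.057 SD, 23% of 0.25.
- b = 0.20, r = 0.8: 0.20 − 0.2 × (0.798 − 0.675) = 0.175 SD, 70% of 0.25.

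**3. Proportion with reduced symptoms.** Simulation with the cut-off and b = 0.10 in treated sites only gives 69.3% treated against 66.6% control at r = 0.5, and 66.8% against 62.7% at r = 0.7, with no treatment effect.

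**4. Check on the mechanism.** With b = 0.25 in both arms the simulated difference-in-differences is 0.0. Only the part that differs between arms and fades biases the result.

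**The case against.** The strongest reply is that the article never says respondents are told their arm. That is right. A reader might infer that allocation is disclosed before baseline, but the text says only that consent comes first and explains participation; the wording of the page is not shown. Disclosure is a likely consequence, not a stated fact.

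A reader might also take the co-written stepped-care invitations as pressure applied before the survey. The text does not support this. They are invitations to the intervention, and Phase 3 places that invitation after scoring. The point does not rest on them.

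Nor can the incentive be said to exist in treated sites only. Controls are promised later access. The symptom criterion under Inclusion criteria and the automatic invitation under Phase 3 are not limited to treated sites, and Exclusion criteria offers the platform where suicidal risk is found, without limit by arm. What remains is a difference in degree: prompt, graded care against delayed, uniform access.

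Larger bias figures follow if no cut-off is applied, but Phase 3 requires symptoms, so those figures do not describe this design.

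Finally, it can be said that this is mere silence in a condensed article about a study that openly calls itself quasi-experimental. That does not dispose of it. The order of consent, survey and care, and the double use of the score, are stated, and declaring non-randomisation does not protect the baseline from this error.

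**Conclusion.** The concern holds as a risk built into the stated sequence, not as a demonstrated bias. Arm is known from the municipality, consent precedes the baseline items, and the baseline score is both the gate to prompt care in treated sites and the pre-measure. A transient rise that is larger in treated sites would pass into the estimate in the favourable direction, and neither differencing nor the planned covariates would remove it. Stable differences in severity are differenced out.

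The article cannot settle the size. With the cut-off and the assumed inputs, differential entry contributes about 0.01 to 0.11 SD at low response and 0.01 to 0.04 SD at 50% response. Over-reporting contributes about 0.06 to 0.18 SD if it occurs in treated sites only and vanishes completely by follow-up. Against a planned 0.25 SD these run from negligible to most of the effect. Confidence is moderate; the low cost of prevention is the main reason to act.

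**What to change.** - Use one truthful survey invitation and one opening consent page, identical in all seven municipalities. State that three surveys are planned, and that any support offered depends on answers and area and may come soon after the first survey or after the last. This wording also stays accurate for respondents without symptoms and for controls.
- In REDCap, show the area's timing and the care offer, with a second consent step, only after the baseline survey is submitted and locked.
- Confirm that the co-written stepped-care invitation goes out only at that point.
- Use the same recruitment contacts over the same weeks in both arms.
- Report response rates and baseline score distributions by arm as a check.

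The referral pathway for people at risk is unchanged.

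The cost is revised wording, a minor ethics amendment and a REDCap branching rule, with no extra participants or staff. A less specific invitation may slightly lower response, and local staff may still disclose an area's status, so concealment is improved, not guaranteed.

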#### Data collection

Quantitative data will be collected through an online survey hosted in Redcap. Data collection will be conducted online. The qualitative and co-design elements of the study will be carried out with beneficiaries and staff of the JeA program via video-conferencing software (Teams).

### Screening questionnaire

To better understand young people’s mental health needs and priorities, the resources available, and any contextual factors relevant to the successful implementation a mental health intervention, we will conduct a brief and focused survey of approximately 150 participants (50 per territory). This survey will use the same screening questionnaires we envisage for the intervention to further test their acceptability with this population. JeA will send the questionnaire via email and text messages and invite participants through phone calls. Beneficiaries will be asked what they think about the survey and how it can be improved. We will make changes according to their feedback. This survey will be administered before the intervention and in two follow-ups (immediately after the intervention and three months after).

### Questionnaire instruments

We will invite all students across the selected PDET municipalities to complete the mental health and human capital survey. The following tools will be used to determine the severity of mental health symptoms and human capital outcomes. (1) *Patient Health Questionnaire – PHQ-9*, which is widely used to assess depression symptoms (28), has been validated for use in Colombia (29, 30) and with low income, limited education populations in rural areas with good results (31, 32). Its internal consistency is 0.80. (2) Anxiety will be assessed with GAD-7 (33). Its internal consistency is 0.90, sensitivity 0.92, and specificity 0.83. (3) A Post-traumatic stress disorder brief screen will also be included PC-PTSD-5 (34). It has a test–retest reliability of 0.83, sensitivity with a score of 3 has a sensitivity of 0.93 m specificity is 0.94. (4) Two questions from the Insomnia Severity Index (35, 36), with a reliability of 0,86, sensitivity of 0.87. (5) AF5 Self-Concept Questionnaire (6) Rosenberg Self-esteem scale (RSE) (37). These questionnaires are widely used by studies where the efficacy of interventions that use digital platforms are examined.

In terms of short-term/immediate assessment of the potential of the intervention to improve human capital, we will look at: school attendance (using administrative data on academic enrolment reports), educational permanence (using administrative data on academic permanence reports, every six months), and academic performance (using administrative data on academic excellence report, every six months). Based on data directly collected as part of the pilot intervention, we will also assess the short-term efficacy of the number of hours spent on average during the past academic period studying weekly, the number of hours that beneficiaries dedicate in this academic period to study weekly and the self-reported grade point average in current and past academic periods. In terms of the longer-term efficacy of the intervention, we will look at: certification (whether completed educational program, based on JeA administrative records) and formal labor market inclusion (whether working in a formal job, based on PILA Administrative Registry). Furthermore, we will also assess the efficacy of the mental health intervention on self-esteem (RSES) and self-concept (AF5).

Figure 3 summarizes the estimated length, activities, and instruments used in each of the phases.

**Figure 3 fig3:**
[figure not shown]
Summary of pilot study phases.

## Data analysis

### Assessing feasibility and acceptability

Feasibility, acceptability, and potential efficacy will be assessed using a “hybrid effectiveness-implementation” approach (38). We will use standard measures across all study sites to facilitate within and cross-site comparisons in efficacy. We will interview a subsample of 5–6 participants in each municipality at month three to explore acceptability qualitatively and learn if different municipalities need different implementation strategies and possible reasons why the intervention failed or succeeded.

### Quantitative analysis of impact

Our primary aim will be to assess the impact of the intervention on our mental health and human capital outcomes. We will use regression analysis with a difference-in-differences design, which compares changes in outcomes before and after intervention measures across participants in treatment and control areas. This approach considers human capital as an outcome embodied in individuals by exploring the variation in individual knowledge (cognitive skills captured by academic performance) and individual abilities (non-cognitive skills acquired as life competencies). Thus, we will look at the magnitude of mental health-based rehabilitation on young adult students across different dimensions of mental health (depression and anxiety, fundamentally), which is considered beneficial due to human capital accumulation.

Since individual observations will be collected in different regions, we will adjust for clustered data. In the absence of treatment randomization that assures that treatment and control groups are exchangeable, this quasi-experimental design helps us to control for time-invariant differences between treatment and control areas by focusing on changes, rather than levels, in outcomes. To address bias from time-varying confounders, we will incorporate controls for time-varying factors in all analyses. We will all report the prevalence of depression, anxiety, and PTSD, along with their commodities and the effectiveness outcome, which will be the proportion of participants with a reduction in their baseline symptoms. To determine the changes in human capital, we will use both administrative and survey data that measure continued JeA program enrolment, accumulated grade point average, and self-reported hours dedicated to study. This will be carried out in STATA-19.

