**Conclusion:**

Findings will help to make conclusions about the feasibility and acceptability of the intervention, and it will assess its effectiveness to improve the mental health and human capital outcomes of beneficiaries. This will enable the identification of strategies to address mental health problems among socioeconomically vulnerable young people that can be adapted to different contexts in in low and middle-income countries.

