## The present study

This study aims to design and pilot a mental health support intervention embedded within the JeA human capital program to achieve better outcomes among beneficiaries, especially those displaced by conflict and the most socioeconomically vulnerable. We aim to develop and test the feasibility and acceptability of a mental health intervention that addresses comorbid mental health problems among beneficiaries of the JeA program. We also aim to make a first evaluation of the impact of potential mental health improvements on human capital outcomes, including educational and employment outcomes.

We will also assess the several outcomes of the mental health intervention to improve the chances of JeA beneficiaries of completing the program and building human capital. Specifically, we will assess preliminary clinical outcomes of the relationship between the mental health intervention, compared to a control group, with dimensions related to human capital formation using a combination of administrative data and survey data collected as part of the intervention, that includes data on academic performance and attendance, as well as data on employment following the completion of the program. We also assess cross-site comparisons in efficacy to see if the effect differs by region. An analysis of the most recent national mental health survey data for conflict victims has not highlighted regional differences in the prevalence of common mental health disorders for victims of the conflict (7). They underscore the need for increased mental health services for this population in their regions. Notwithstanding, we will include in our statistical analysis tests for regional differences, comparing against control groups.

The project has three main research questions leading to methodological, empirical, and policy-related contributions:

Can a stepped-care mental health with a digital component improve young people’s mental health and human capital in conflict-affected areas?Can this stepped-care mental health intervention improve young people’s chances of succeeding in their training and educational outcomes?Is a stepped-care mental health with a digital component feasible and acceptable for inclusion in the JeA program in conflict-affected areas in Colombia?

We expect to address these aims in a period of 36 months (3 years).

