### Study design, sample, and recruitment

#### Sample size

As a pilot study with no pre-specified effect size hypothesis, it is not relevant to estimate a sample size for hypothesis testing. However, to carry out preliminary analysis of impact, we defined the sample size as follows: assuming an intraclass correlation coefficient of 0.04, an effect size of 0.125 (index f) equivalent to Cohen’s d = 0.25, with a significance level of 5% and a statistical power of 80%, the minimum sample required would be 501 participants (167 per site, of three locations). Our goal is to recruit a minimum of 170 participants from each site, given an expected moderately high attrition rate.

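### Impact is ranked as the primary aim in one section and as a preliminary add-on in others, and the stated design inputs do not support the effectiveness conclusions promised

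*Protocol article*

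**What the plan says.** The article ranks its aims in more than one way.

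- **Quantitative analysis of impact:** "Our primary aim will be to assess the impact of the intervention on our mental health and human capital outcomes". The analysis is a difference-in-differences regression. The section acknowledges that treatment was not randomised.
- **The present study:** "We aim to develop and test the feasibility and acceptability of a mental health intervention that addresses comorbid mental health problems", followed by "We also aim to make a first evaluation of the impact of potential mental health improvements on human capital outcomes". The same section then lists three main research questions. The first two ask whether the intervention improves outcomes; feasibility and acceptability come third.
- **Sample size:** "As a pilot study with no pre-specified effect size hypothesis, it is not relevant to estimate a sample size for hypothesis testing". The next sentence begins "However, to carry out preliminary analysis of impact, we defined the sample size as follows" and goes on "assuming an intraclass correlation coefficient of 0.04, an effect size of 0.125 (index f) equivalent to Cohen’s d = 0.25", with 5% significance and 80% power, giving 501 participants (167 at each of three locations).
- **Assessing feasibility and acceptability:** efficacy is called potential and is assessed together with feasibility and acceptability under a hybrid effectiveness-implementation approach.
- **Abstract (Conclusion) and Discussion:** "it will assess its effectiveness to improve the mental health and human capital outcomes of beneficiaries". Phase 3 says the results will show whether clinical, educational and employment prospects improve.

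Study design names three treatment and four control municipalities.

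**The concern.** A primary aim determines which result leads the report and how firmly it is stated. Here one section gives that place to impact, while others give it to feasibility and acceptability and call the impact work preliminary. An analyst or report writer could follow either, and an analysis plan taking its primary aim from this text would have to choose.

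What is at stake is the strength of the final claim. If impact leads and the wording on effectiveness is followed, an estimate from seven non-randomised municipalities may be presented as a finding that the intervention works or does not work. The Discussion links the findings to government adoption and to policy, so an over-firm reading in either direction would matter.

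**Working it through.** **1. The passages side by side.** Impact as the primary aim (Quantitative analysis of impact) does not fit with impact as something the study also evaluates for the first time (The present study), or with a preliminary analysis in a pilot (Sample size). Promised conclusions on effectiveness (Abstract, Discussion) do not fit with potential efficacy (Assessing feasibility and acceptability). Two further places add to this. Research questions 1 and 2 ask about improvement before feasibility is mentioned. The Sample size section calls sizing for a test not relevant and then sizes for one. This inconsistency needs no arithmetic.

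**2. The plan's own figure.** Inputs from Sample size: d = 0.25, alpha 5% (two-sided assumed, as sidedness is not stated), power 80%. For two groups of independent participants:

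n per group = 2 × (1.960 + 0.842)² / 0.25² = 251.2, rounded up to 252, so 504 in total.

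This is within 1% of the stated 501, and power at 501 is 79.9%. The figure reproduces only when participants are treated as independent. The stated ICC of 0.04 has no effect in it.

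**3. Power with the stated ICC, post-only comparison.** Three against four municipalities, m participants in each, total variance 1:

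SE = √[(0.04 + 0.96/m) × (1/3 + 1/4)]

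Numbers in the control municipalities are not stated, so two readings are shown. Power for d = 0.25 is given for a normal reference and for a t reference with 7 − 2 = 5 degrees of freedom.

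| Reading | m | SE | 0.25/SE | Power, normal | Power, t (5 df) |
|---|---|---|---|---|---|
| 501 spread over seven | 71.6 | 0.177 | 1.42 | 29% | 21% |
| 167 in each of seven | 167 | 0.163 | 1.53 | 33% | 24% |
| Unlimited m | ∞ | 0.153 | 1.64 | 37% | 27% |

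The limit is set by the number of municipalities. More participants in each one barely help.

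**4. Difference-in-differences.** This is the planned analysis. Its precision depends on c, the correlation over time of the municipality effects, and i, that of the individual effects. The article gives neither. With one measurement before and one after:

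SE = √[2 × (0.04(1 − c) + 0.96(1 − i)/m) × (1/3 + 1/4)]

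Purely as an illustration, with i assumed between 0.5 and 0.6 and t with 5 df:

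| Assumed c | Power, m = 71.6 | Power, m = 167 |
|---|---|---|
| 0.5 | 21–22% | 24% |
| 0.8 | 34–37% | 44–45% |
| 0.9 | 44–49% | 61–65% |
| 1.0 | 62–72% | 93–97% |

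The answer runs from little better than post-only to above 80%, depending on values that are not given. These figures ignore the attrition that the Sample size section expects.

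**The case against.** Four objections deserve weight.

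- **The sentence may be local.** It opens a section on impact, directly after a separate section on feasibility, and may name the primary aim of that analysis only. This is possible, but the text does not say so. Even on that reading, the effectiveness wording in the Abstract, Phase 3 and Discussion remains.
- **Impact is a genuine aim.** Research questions 1 and 2 and the hybrid approach support this. It stands: the documents do not show that impact is the wrong aim. They show that its rank and firmness are not settled.
- **The limits are openly stated.** The article acknowledges the lack of randomisation and specifies no decision rule based on a p-value. A reader might infer that a significance test will be the headline result; the article does not say that.
- **The power figures rest on assumptions.** They do, because control numbers and correlations over time are not stated. The inconsistency does not depend on them.

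Two stronger readings are tempting. One is that the article declares its design not to be for hypothesis testing. It says only that estimating a sample size for testing is not relevant, and then gives a significance level and a power. The other is that the feasibility result decides on a later full trial. No such trial is mentioned; the Discussion speaks of long-term adoption within the Youth in Action program.

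**Conclusion.** The point holds as an inconsistency in the ranking of aims and in the firmness of the promised conclusions. The stated inputs do not support a firm conclusion about d = 0.25 in either direction. Post-only power is about 21% to 33% at ICC 0.04 with three against four municipalities, assuming equal cluster sizes, a two-sided 5% test and no attrition.

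A reader might go further and infer that the difference-in-differences analysis is itself underpowered. The article does not allow that conclusion: power depends on correlations that it does not report, and it could be adequate if municipality effects were almost constant over time. Even then, a positive estimate would come from seven selected, non-randomised areas and would remain open to time-varying differences between them.

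**What to change.** State one ranking of aims throughout. Replace the first sentence of Quantitative analysis of impact with wording such as:

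> The impact analysis is preliminary. Results are reported as difference-in-differences estimates with 95% confidence intervals that allow for the seven municipalities as clusters. No conclusion of effectiveness, or of no effect, is drawn from p-values.

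Then align with it:

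- the wording on effectiveness or improvement in the Abstract (Conclusion), Phase 3 and Discussion;
- research questions 1 and 2 in The present study;
- the sentence on significance level and power in Sample size.

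Changing the Sample size section alone would leave the conflicting aim in place. If the sponsor prefers impact as a main aim under the hybrid approach, the sample size would need a justification that includes the clustering and the assumed correlations over time.

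The cost is wording and a less ambitious headline claim. Recruitment, data collection and the regression approach stay as they are.
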